### In the event of detection of metastases

If a suspected metastasis is detected in radiological examinations and then verified with a biopsy, the patient will be referred by their physician to an oncology clinic in their home region. This is a standard clinical routine and will not be impacted by this trial. The oncology clinic will make a decision regarding next steps to investigate, examine, and treat the metastases. Patients with metastases typically receive systemic chemotherapy, immunotherapy with so-called checkpoint inhibitors, and/or regional perfusion treatment of the liver where high doses of chemotherapy are injected into the liver’s circulatory system. These treatments are demanding for patients and can result in side effects such as fatigue, susceptibility to infection, dry mucous membranes, and pain. The average survival following metastasis detection is about 1 year. Metastasis detection does not alter the melatonin doses or treatment instructions in this trial. Melatonin given at a dose of 20 mg at 10 pm has shown particularly positive effects in advanced stages of cancer in earlier studies [10].

It has also been reported that systemic chemotherapy is more easily tolerated in patients who are simultaneously treated with melatonin, particularly in regard to neurotoxicity, thrombocytopenia, weight loss, and asthenia [44]. Furthermore, there are fewer cases of alopecia (hair loss) and infection in patients taking 20 mg of melatonin at 10 pm while undergoing radiotherapy [45]. If participants in this trial take melatonin from the time that their metastases are detected, the metastases will be included in both the intention-to-treat and the per-protocol analysis. Survival in the melatonin group following metastasis detection will therefore be counted in the patients still taking melatonin.

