### Withdrawal

Subjects may voluntarily withdraw from the trial at any time without impacting further standard treatment. The principal investigator reserves the final right to terminate the trial for a specific subject due to unacceptable side effects or poor compliance. If a subject terminates their participation in this trial, their trial-specific ID will not be re-used. They will not be able to re-join the trial. No further data will be collected; however, data that has already been collected will be used for the final analysis of the trial. Participants who withdraw within 6 months following randomization will be replaced by newly recruited and randomized patients with a ratio of 1:1, i.e., if two participants withdraw from the trial within 6 months, they will be replaced by two new participants. Patients who withdraw from the trial after 6 months following randomization will not be replaced.

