### Statistical analysis

We will be analyzing our data according to “intention to treat” where all participants randomized to either the melatonin or control group are included in the said group even if some terminate their participation in the trial or are excluded from the trial later on. We will at the same time analyze our data “per protocol” where the participants who terminate their participation during the trial or are noncompliant to melatonin treatment are excluded from the analysis.

To answer our primary and secondary objectives, we will use both the chi-square test and the Log-rank test of cumulative survival with associated 95% confidence intervals and *p*-values. Relative risk will be calculated as the probability of metastasis in the melatonin group divided by the risk of metastasis in the control group.

*P* values less than 0.05 will be considered significant, and all tests will be double-tailed, or two-sided.The Shapiro–Wilk test will be used to confirm if our continuous data is normally distributed.A Student’s *t*-test will be used to compare the differences in normally distributed continuous data within the melatonin and control groups, respectively. Data found not to be normally distributed data will be compared using the Mann–Whitney *U*-test.In order to compare the risk of death and metastasis between the melatonin and control group, we will also use a Cox Regression, adjusted for covariates such as tumor size, T category, cell type, presence of extra scleral growth, presence of extracellular matrix patterns, and BAP-1 expression.

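### The per-protocol set can lose melatonin patients, with their metastases, for stopping tablets after the metastasis was found

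*Protocol article*

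**What the plan says.** Two sections of the protocol article bear on this point.

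**In the event of detection of metastases.** Tablet instructions stay in force after the event: "Metastasis detection does not alter the melatonin doses or treatment instructions in this trial". The section then says "If participants in this trial take melatonin from the time that their metastases are detected, the metastases will be included in both", where the last word refers to intention to treat and per-protocol, and draws a consequence for survival: "Survival in the melatonin group following metastasis detection will therefore be counted in the patients still taking melatonin".

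**Statistical analysis.** For intention to treat, "all participants randomized to either the melatonin or control group are included in the said group even if some terminate their participation". For per-protocol, "the participants who terminate their participation during the trial or are noncompliant to melatonin treatment are excluded from the analysis". The second rule has no cut-off at the primary event. Both analyses are to be run alongside each other with significance at 0.05 two-sided, and neither is named as the one that carries the conclusion.

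The Withdrawal section adds that "data that has already been collected will be used for the final analysis of the trial".

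**The concern.** A metastasis is the primary event. Whether the patient goes on taking tablets afterwards cannot have caused or prevented it, yet under these rules it can decide whether patient and event stay in the per-protocol analysis. Because the instructions are unchanged after detection, a patient who stops then counts as non-compliant.

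Stopping may well be linked to the event. Of the oncology treatment given after detection, the article says "These treatments are demanding for patients and can result in side effects such as fatigue". It puts average survival from that point at about one year. Non-compliance with melatonin can arise only in the melatonin arm, so controls face no matching tablet condition.

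If stopping is commoner after metastasis than without it, the melatonin arm loses events faster than non-events, and the per-protocol risk falls even if melatonin does nothing. Survival after metastasis is exposed in the same way: patients who stop because they are deteriorating are left out of the melatonin arm, while comparable controls stay in.

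**Working it through.** **1. The plan's own figure.** Inputs from Sample size: 30% v 60%, alpha 0.05 two-sided, power 80%. With pooled variance and no continuity correction, n = [1.960 × √(2 × 0.45 × 0.55) + 0.842 × √(0.30 × 0.70 + 0.60 × 0.40)]² / 0.30² = (1.379 + 0.565)² / 0.09 ≈ 42 per group. The stated 42 reproduces and is untouched by this point.

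**2. Expected per-protocol relative risk when melatonin has no effect.** Inputs: 50 per arm (the target) and a 60% risk in both arms (the planned control risk), so 30 patients with metastasis and 20 without in each arm. Let q be the share of melatonin patients with metastasis who are excluded for stopping after it, and r the share of metastasis-free melatonin patients excluded for non-compliance. **The article gives neither, so both are assumptions.** No controls are excluded in this step.

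Risk kept = 30(1 − q) / [30(1 − q) + 20(1 − r)], and RR = risk kept / 0.60.

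| q | r | Events / patients kept | Risk | RR | Chance of p < 0.05 favouring melatonin |
|---|---|---|---|---|---|
| 10% | 10% | 27/45 | 60.0% | 1.00 | 2.6% |
| 20% | 10% | 24/42 | 57.1% | 0.95 | about 5% |
| 30% | 20% | 21/37 | 56.8% | 0.95 | about 5% |
| 30% | 10% | 21/39 | 53.8% | 0.90 | about 9% |
| 50% | 10% | 15/33 | 45.5% | 0.76 | about 26% |
| 20% | 30% | 24/38 | 63.2% | 1.05 | about 1% |

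The last column comes from simulated trials of 50 per arm with the uncorrected chi-square test; the nominal figure is 2.5%. Bias arises only from the gap between q and r, and its sign follows the sign of that gap.

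**3. Controls who leave.** Ending participation removes patients from either arm. Take q = 30%, r = 10%, and suppose also that 10% of controls with metastasis leave and are excluded. The control risk kept is 27/47 = 57.4%, so RR = 53.8/57.4 = 0.94. The chance of a false positive favouring melatonin drops from about 9% to about 5%.

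**4. Is it enough to judge compliance only up to detection, or to 5 years if there is none?** No. Metastasis-free patients are then watched for longer and have more time to be excluded. Assume constant hazards: λ = −ln(0.4)/5 for metastasis and μ = −ln(1 − c)/5 for non-compliance, where c is five-year non-compliance. The share of the arm kept with an event is λ/(λ + μ) × (1 − e^(−5(λ+μ))), and without one e^(−5(λ+μ)).

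- c = 10%: 0.574 and 0.360, RR = (0.574/0.934)/0.60 = 1.02
- c = 30%: 0.518 and 0.280, RR = (0.518/0.798)/0.60 = 1.08
- c = 50%: 0.455 and 0.200, RR = (0.455/0.655)/0.60 = 1.16

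That repair replaces one bias with a bias against melatonin. Censoring in a time-to-event analysis avoids it.

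**The case against.** **Intention to treat.** A reader might infer from the detection section that metastases also drop out of intention to treat when tablets are stopped. The documents do not support this. The sentence says if, not only if. Statistical analysis keeps all randomised participants, who "are included in the said group even if some terminate their participation in the trial or are excluded from the trial later on", and the Withdrawal section retains data already collected. What remains is wording to reconcile.

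**What the sentence is about.** It could mean patients on tablets at the time of detection, and it leads into survival after metastasis, a secondary outcome. The sentence on patients still taking melatonin speaks against the first reading. In any case the per-protocol rule in Statistical analysis is enough by itself to exclude patients for stopping after the event.

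**Controls.** A reader might infer that every control metastasis is kept. It is not: a control who metastasises and then leaves is also excluded, which reduces the bias (step 3). Only the tablet condition is confined to the melatonin arm.

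**Size.** The stopping rates are assumed, and the direction can reverse. The article itself cites reports that chemotherapy is better tolerated with melatonin, which could keep patients on tablets after metastasis. This objection stands, and it is why the result is given as a range over both q and r.

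**Left to the analysis plan.** A compliance threshold may properly be set there. The fault here is a stated rule that looks past the event, not a missing detail.

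**Conclusion.** The point holds for the per-protocol analysis of metastasis and for survival after metastasis. Both let tablet-taking after the event decide who is counted, through a condition that only the melatonin arm can fail. If stopping is commoner after metastasis than without it, both comparisons lean towards melatonin.

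With a 60% risk in both arms, the null per-protocol relative risk runs from 0.95 (q = 20%, r = 10%) through 0.90 (30%, 10%) to 0.76 (50%, 10%). It is 1.00 when q = r and 1.05 at 20% and 30%. These figures rest on assumed stopping rates and on no exclusions among controls. The effect on survival after metastasis is not quantified, since that would need further assumptions about who stops and when.

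Intention to treat is not shown to be affected, and the sample size is unchanged. Severity is moderate: nothing in the article rests the primary conclusion on per-protocol, but nothing ranks it below intention to treat either.

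**What to change.** 1. **In the event of detection of metastases:** state that every metastasis counts in the randomised arm in the intention-to-treat analysis whatever the tablet intake, and that survival after metastasis is analysed by randomised arm without dropping patients who stop tablets.
2. **Statistical analysis:** state that stopping tablets or ending participation after detection removes neither the patient nor the event from the per-protocol analysis. Analyse per-protocol metastasis as time to event with the log-rank and Cox methods already planned, censoring at first non-compliance or withdrawal before metastasis, instead of as a proportion after exclusions. Give controls a matching rule: censor at documented melatonin use before metastasis.
3. **Statistical analysis:** state that intention to treat carries the primary conclusion and that per-protocol is supportive.

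The cost is a few sentences. Compliance is already asked at one month and every six months, metastasis is recorded from patient charts, and the investigators can already see melatonin prescribed outside the trial. No visit, dose or sample size changes. There are two downsides: the per-protocol result may look less favourable to melatonin, and censoring at non-compliance assumes that non-compliance is unrelated to the risk of metastasis, which should be stated with the result.

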### Outcomes

The primary outcome is the number of patients which develop metastasis in the melatonin group vs. the control group. This will be evaluated as a relative risk (RR), with a 95% confidence interval. The secondary outcomes include the following: Overall survival 5 years from randomization in the melatonin group vs. control group, evaluated with Kaplan-Meier curves and the Log-rank test.Overall survival after detection of metastases in the melatonin group vs. control group, was evaluated with Kaplan-Meier curves and the Log-rank test.Hazard for having developed other cancers within 5 years from randomization in the melatonin group vs. control group, evaluated as Cox regression hazard ratio (HR).Number of patients with AE and SAE in the melatonin group vs. control group, assessed by CTCAE and evaluated as relative risk (RR) with a 95% confidence interval.

Other outcome measures:Interim analysis: number of patients developing metastasis within 3 years in the melatonin group vs. control group, evaluated as relative risk (RR), with 95% confidence interval.Interim analysis: overall survival in 3 years in the melatonin group vs. control group, evaluated with Kaplan-Meier curves and the Log-rank test.

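### The rule for counting survival after metastasis depends on tablet use in the melatonin group only and conflicts with the intention-to-treat rule; if followed, it can favour melatonin without any drug effect

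*Protocol article*

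**What the plan says.** Four parts of the protocol article bear on who is counted.

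- **In the event of detection of metastases.** Detection leaves the trial treatment as it was: "Metastasis detection does not alter the melatonin doses or treatment instructions in this trial". For participants who take melatonin from the time of detection, "the metastases will be included in both the intention-to-treat and the per-protocol analysis". The section then concludes: "Survival in the melatonin group following metastasis detection will therefore be counted in the patients still taking melatonin". It gives no counting condition for controls, who have no tablets.
- **Outcomes.** The secondary outcome is a plain comparison of the groups: "Overall survival after detection of metastases in the melatonin group vs. control group, was evaluated with Kaplan-Meier curves and the Log-rank test".
- **Statistical analysis.** Under intention to treat, "all participants randomized to either the melatonin or control group are included in the said group even if some terminate their participation". A per-protocol analysis runs alongside it, in which those who end participation or are "noncompliant to melatonin treatment are excluded from the analysis". Two-sided p-values below 0.05 count as significant.
- **Withdrawal.** After a subject's participation ends, no more data are collected. Poor compliance is one ground on which the investigator may end it.

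**The concern.** The sentence on patients still taking tablets is the only counting rule specific to this outcome. It conflicts with the general intention-to-treat rule, and two analysts who each follow one of the two sections would count different patients.

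The choice is not neutral. Whether a patient is still on tablets after detection is settled after randomisation. The protocol describes treatment for metastases as demanding and puts survival at about a year, so it is plausible, though not stated, that patients who deteriorate stop first. If they are removed or censored at that point, deaths disappear from the melatonin arm and nothing comparable happens among controls. The log-rank test could then favour melatonin on a listed secondary objective with no effect of the drug.

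**Working it through.** **1. The plan's own figure.** The protocol gives no figure for this outcome. Its one calculation is for the primary outcome (30% v 60%, two-sided alpha 0.05, power 80%):

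n = [1.96·√(2·0.45·0.55) + 0.8416·√(0.3·0.7 + 0.6·0.4)]² / 0.30² = (1.379 + 0.565)² / 0.09 ≈ 42 per group.

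This reproduces the stated 42 and does not depend on the tablet rule.

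**2. Inputs.**
- From the protocol: 50 patients per arm; 60% metastases gives 50 × 0.60 = 30 patients, and the planned 30% gives 50 × 0.30 = 15.
- From the protocol: "The average survival following metastasis detection is about 1 year". This is modelled as exponential with median 12 months in both arms, so there is no true effect. The mean is 12 / ln 2 = 17.3 months.
- Assumed, because the protocol gives nothing: the share q of melatonin patients with metastases who stop because of illness, the interval L between stop and death, and administrative censoring uniform over 0.5 to 6 years.

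**3. Approximate size if follow-up is cut at the stop.** A share q of deaths is lost, and each of those patients loses L months of follow-up. Ignoring administrative censoring:

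rate ratio ≈ (1 − q) / (1 − q·L/17.3)

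- q = 20%, L = 1: 0.80 / 0.988 = 0.81
- q = 40%, L = 1: 0.60 / 0.977 = 0.61

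The ratio depends mainly on q. With a mean of 12 months in place of 17.3, the first line is 0.80 / 0.983 = 0.81.

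**4. Simulation under no effect** (8,000 trials per setting, two-sided log-rank at 5%, stop one month before death, stop date known):

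| Melatonin v control patients with metastases | Share stopping | Rate ratio | False significance |
|---|---|---|---|
| 30 v 30 | 20% | about 0.8 | 11% |
| 30 v 30 | 40% | about 0.6 | 30 to 32% |
| 15 v 30 | 20% | about 0.8 | 8% |
| 15 v 30 | 40% | about 0.6 | 19 to 20% |

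Without the rule, false significance is about 5 to 6%. Nearly all of the excess favours melatonin.

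**5. Other ways of applying the rule.** The first two items come from a second simulation: 50 per arm, 60% metastases in both, follow-up to 5 years and 4,000 trials per setting. False benefit there means significance in favour of melatonin, nominally 2.5%.
- Stoppers dropped altogether, stopping two months before death, q from 10% to 50%: hazard ratio 0.97 to 0.80, false benefit 3.5% to 9.0%.
- Status fixed at detection, earlier stopping unrelated to prognosis: hazard ratio about 1.00 to 1.02, false benefit about 2 to 3%.
- Stops recognised only if a six-monthly call falls between stop and death, in the setting of step 4. With L = 1 a call does so about 1 time in 6, so q = 40% acts like 40% / 6 = 6.7%, and the ratio is about 0.933 / 0.996 = 0.94. Simulated with 30 v 30: 0.93 to 0.94 and about 6% false significance.

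**6. With every patient with metastasis counted in both arms** (second simulation): hazard ratio 1.00 and two-sided error 5.2% at 60% metastases in both arms; 1.02 and 6.4% at 30% v 60%.

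**The case against.** The sentence can be read as explanation, not as a filter. Treatment continues past metastasis, and therefore survival after detection is observed on treatment. The sentence before it refers to tablet use from the time of detection, which points towards fixing status at that moment; step 5 shows almost no bias then if earlier stopping is unrelated to prognosis. The formal sections set a plain group comparison under intention to treat, and if they govern, the problem disappears. The protocol gives no stopping rate and does not say that sicker patients stop. Compliance is asked by telephone at one month and then every six months, so many late stops might never be recorded.

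Much of this stands. A reader might infer that the plan counts only on-tablet melatonin patients against all controls, and so will produce a false survival benefit. The documents do not go that far: neither restriction is written in those terms, the general rule points the other way, and the larger error rates need illness-related stopping shortly before death with known stop dates.

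What does not fall away is the conflict. The wording ties the intention-to-treat analysis, not just the per-protocol one, to tablet use. It speaks of patients still on tablets after detection, and no text says which section prevails.

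**Conclusion.** The concern holds as a conflict between stated rules, with a possible bias whose size is conditional. Followed as written, the metastasis section conditions one arm of a secondary comparison on a post-randomisation state that may be linked to prognosis.

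With no true effect and 30 v 30 patients, the result ranges from essentially no bias to a rate ratio of about 0.8 with 11% false significance (20% stop) or about 0.6 with about 30% (40% stop). The upper figures assume censoring at a known stop one month before death. The low end applies if status is fixed at detection, stopping is unrelated to prognosis, or stops are known only from six-monthly calls.

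It should be corrected, but it does not threaten the main result: the primary relative risk, the 42 per group and overall survival from randomisation are untouched. Even when corrected, the comparison covers only patients who metastasise, a subset formed after randomisation, and should be read as descriptive.

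**What to change.** Delete the sentence on patients still taking melatonin, and remove the tablet condition for the intention-to-treat analysis in the sentence before it. State instead that survival after detection is analysed for every patient with metastasis in the arm as randomised, from detection to death or last available follow-up, with no restriction to, or censoring at, melatonin use. Label any on-treatment figure supplementary and descriptive.

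Align the Withdrawal section: stopping tablets alone should not count as a withdrawal that ends data collection, and patients who do leave the trial are censored at their last collected data. Without this, deaths after a compliance-based termination would still be missing from the melatonin arm.

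The cost is a few sentences, with no change to treatment or visits. Follow-up data continue for patients who stop tablets but remain in the trial, and deaths after a true withdrawal stay unobserved. The change should be made before outcome data are examined, because choosing between the two sections afterwards could itself decide the result.

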### Withdrawal

Subjects may voluntarily withdraw from the trial at any time without impacting further standard treatment. The principal investigator reserves the final right to terminate the trial for a specific subject due to unacceptable side effects or poor compliance. If a subject terminates their participation in this trial, their trial-specific ID will not be re-used. They will not be able to re-join the trial. No further data will be collected; however, data that has already been collected will be used for the final analysis of the trial. Participants who withdraw within 6 months following randomization will be replaced by newly recruited and randomized patients with a ratio of 1:1, i.e., if two participants withdraw from the trial within 6 months, they will be replaced by two new participants. Patients who withdraw from the trial after 6 months following randomization will not be replaced.

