#### Intervention

Participants will be equally randomized into two groups: the melatonin group (treated with 20-mg melatonin each night for 5 years) or the control group (no intervention). When a patient is recruited and randomized to the melatonin group, blood samples will be ordered by a licensed physician regarding creatinine, electrolytes (sodium, potassium), and alanine transaminase (ALAT). This blood test will be repeated after 2 and 4 years (Fig. 1 and Tables 1 and 2).

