^b^Evaluation of the proportion of subjects with metastases is performed through data collection via registries, chart documentation, and statistical work. It therefore does not require subjects’ active participation

**Table 2 Tab2:** Flowchart

**Time**	**Screening** − 30 days before 1 m visit	**Month 1** ± 7 days	**Month 6** ± 4 weeks	**Year 1** ± 4 weeks	**Year 1.5** ± 8 weeks	**Year 2** ± 8 weeks	**Year 2.5** ± 8 weeks	**Year 3** ± 8 weeks	**Year 3.5** ± 8 weeks	**Year 4** ± 8 weeks	**Year 4.5** ± 8 weeks	**Year 5** ± 8 weeks
Inclusion/exclusion	x											
Informed consent	x											
Randomization melatonin/control group	x											
Medical history, current medication	x											
Medication instruction	x											
Radiological examination—liver			x	x	x	x	x	x	x	x	x	x
Radiological examination—thorax and abdomen	x											
Blood samples	x					x				x		
AE and SAE, prescription compliance		x	x	x	x	x	x	x	x	x	x	x
End of study												x

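### Data collection stops when participation ends, which conflicts with the intention-to-treat analysis and leaves avoidable gaps in the 5-year metastasis outcome

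*Protocol article*

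**What the plan says.** The article's Withdrawal section lets subjects leave at any time and adds: "The principal investigator reserves the final right to terminate the trial for a specific subject due to unacceptable side effects or poor compliance". For a subject who terminates participation it then states: "No further data will be collected; however, data that has already been collected will be used for the final analysis of the trial". Leavers within 6 months of randomisation are replaced; later ones are not.

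The Statistical analysis section defines intention to treat (ITT) so that "all participants randomized to either the melatonin or control group are included in the said group even if some terminate their participation", and extends this to people excluded later. A parallel per-protocol analysis leaves out those who stop participating or do not comply.

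The primary outcome is the number of patients with metastasis in each arm, 5 years after randomisation. The Outcomes section says: "This will be evaluated as a relative risk (RR), with a 95% confidence interval".

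On data sources, footnote b to Table 1 says: "Evaluation of the proportion of subjects with metastases is performed through data collection via registries, chart documentation, and statistical work". It adds that subjects need take no active part. The Clinical effects section takes metastasis, death and other cancers from patient charts. Trial design and Follow-up describe imaging and eye follow-up as routine care for all uveal melanoma patients, with eye follow-up lifelong.

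**The concern.** An RR of 5-year metastasis needs a 5-year status for everyone in the denominator. Under the withdrawal rule, a patient who leaves without metastasis has none. That patient can be listed in the randomised arm, but the outcome has to be assumed, imputed or left out. An analysis plan can choose among these options; it cannot recover data the protocol says will not be collected.

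The loss need not be balanced. Control has no study treatment to comply with and no melatonin side effects, so termination by the investigator on those two grounds would fall essentially on the melatonin arm. The trial is open-label, so the decision is made with the allocation known. At stake is the protection of randomisation for the primary RR, and also for overall survival and other cancers, which rely on the same records.

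**Working it through.** **The plan's own figure.** With 30% versus 60%, two-sided alpha 0.05, 80% power and pooled variance (Sample size section):

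n = [1.960·√(2·0.45·0.55) + 0.842·√(0.3·0.7 + 0.6·0.4)]² / 0.30² = (1.379 + 0.565)² / 0.09 ≈ 42 per arm.

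The stated 42 reproduces. The target of 50 leaves a margin of 8 per arm (8/50 = 16%).

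**Model.** Inputs from the article: 50 per arm and 60% control risk at 5 years. Assumed: the same 60% in both arms (true RR 1), a constant hazard, and loss unrelated to risk. The article gives no loss rates or timings, so all of those below are assumptions too.

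- Hazard: λ = −ln(0.40)/5 = 0.183 per year.
- Observed risk in an arm that loses a fraction w: (1 − w)·0.60 + w·m, where m is the chance that metastasis is seen before leaving. Later events are counted as none.
- Loss spread evenly over 0 to 5 years: m = 1 − 0.60/(5·0.183) = 0.345. Loss at the very start: m = 0.

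**Losses in both arms.**

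| Melatonin vs control lost | Timing | Calculation | RR |
|---|---|---|---|
| 8 vs 2 | even over 5 years | (0.84·0.60 + 0.16·0.345)/(0.96·0.60 + 0.04·0.345) = 0.559/0.590 | 0.95 |
| 12 vs 2 | even over 5 years | (0.76·0.60 + 0.24·0.345)/0.590 = 0.539/0.590 | 0.91 |
| 8 vs 2 | at the start (extreme) | 0.84/0.96 | 0.88 |
| 12 vs 2 | at the start (extreme) | 0.76/0.96 | 0.79 |
| 10 vs 10 | any | same loss in both arms | 1.00 |

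**One-sided loss.** Here loss begins at 6 months, because earlier leavers are replaced.

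- 16% from melatonin only, spread over 0.5 to 5 years: m = 0.379, so RR = (0.504 + 0.061)/0.60 = 0.94.
- 16% from melatonin only, all at 1 year: m = 0.167, so RR = 0.531/0.60 = 0.885.
- Exact enumeration of the chi-square test at 50 per arm gives the chance of a false significant result favouring melatonin. It is 2.6% with complete follow-up, 5.8% with the spread loss and 11.1% with loss at 1 year.
- 20% from control only: RR 1.08 (spread) or 1.17 (at 1 year), against melatonin.

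**Leaving patients out instead.** Suppose 20% of the melatonin arm is dropped entirely and those patients have risk r. The rest have risk (0.60 − 0.20·r)/0.80.

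- r = 80%: 0.55, RR 0.92.
- r = 40%: 0.65, RR 1.08.
- If only the event-free leavers among the 20% are dropped, RR is 1.03 (loss at 1 year) to 1.06 (spread).

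**Scale.** The standard error of log RR at 30/50 in each arm is √(2·0.40/30) = 0.163. The spread-loss shifts for 8 vs 2 and 12 vs 2 are ln 0.948 = −0.053 and ln 0.914 = −0.090, or about 0.3 and 0.6 standard errors.

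**The case against.** Several points on the other side have force.

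- **Investigator termination.** The stop-collection sentence follows words about a subject ending participation. Its extension to termination by the investigator is the natural reading of one continuous paragraph, but it is not spelled out. The per-protocol definition also names non-compliance separately from leaving, so a non-compliant patient can remain in the trial. This stands as a limit on the point, and the ambiguity itself needs settling.
- **Other analyses.** A reader might infer that ITT is impossible, or that leavers have to be scored metastasis-free or dropped. Neither follows. The Statistical analysis section also plans log-rank and Cox analyses, which can censor at withdrawal, and missing-outcome rules may sit in an analysis plan not shown. Such censoring may still be informative, and the simple RR has no equivalent.
- **Direction.** A reader might infer that loss will be unequal and the RR biased toward melatonin. The article gives no withdrawal rates by arm, and controls in an open-label trial may leave too. The calculations show bias in either direction, or none.
- **Size.** The start-of-trial figures ignore replacement within 6 months. Replacement does not restore the outcomes of those who left, but these figures remain extremes. A bound built from 8 unknown per arm at design rates runs from 12.6/33.2 = 0.38 to 20.6/25.2 = 0.82. It requires every lost patient in one arm to metastasise and none in the other, and says nothing about direction. The margin of 8 is an allowance, not a forecast.
- **Existing separation.** The exclusion criteria already let a participant who starts certain interacting drugs pause melatonin without leaving, and the safety text allows temporary interruption. It would be wrong to say that the plan never separates drug from follow-up. The gap concerns the end of participation.

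**Conclusion.** The Withdrawal and Statistical analysis sections conflict and must be reconciled. Followed as written, the withdrawal rule discards 5-year metastasis status that the article's own data sources could supply, and it affects the primary endpoint. This rests on the text and needs no assumption about loss rates.

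The effect on the RR is conditional. If more melatonin than control patients leave and their later events count as none, the RR moves toward melatonin: about 0.95 to 0.91 in the assumed spread-loss examples, with 0.88 and 0.79 as extremes. With equal loss unrelated to risk it stays near 1.00. With loss mainly from control, or with some ways of dropping patients, it moves against melatonin. The documents support a risk of bias of uncertain direction and modest size under spread loss, not a predicted bias. The point still needs correcting before outcomes are lost, because they may not be recoverable later.

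**What to change.** Amend the Withdrawal section so that the end of melatonin, or of active participation, is distinct from withdrawing consent to the use of records. For everyone except those who refuse further use of records, keep collecting metastasis, vital status and other-cancer data from charts and registries to 5 years after randomisation. This should apply whether the subject or the investigator ended participation. Analyse all of them in their randomised arm. The analysis plan can then state how the few who refuse enter the RR, with a sensitivity analysis.

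The clinical criteria for stopping melatonin need no change, and no visits are added. The cost is one amended paragraph, one consent-form sentence and a little more chart and registry abstraction.
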